### Hypotheses

1. Vitamin D_3_ supplementation (2,000 IU/d vs. 40,000 IU/m) for 6 months will result in significantly improved overall vitamin D status and improved markers of bone health in adult patients with diabetic nephropathy. Serum 25(OH)D will increase by a minimum of 25–50 nmol/L post-supplementation. Markers of bone resorption will decrease and markers of bone formation will increase after 6 months of vitamin D_3_ supplementation when compared to baseline levels.

2. Monthly dosing of vitamin D_3_ (40,000 IU/m) over 6 months will result in improved patient adherence and satisfaction with vitamin D_3_ supplementation when compared to daily dosing of vitamin D_3_ (2,000 IU/d) resulting in improved overall vitamin D status, bone health parameters, and quality of life.

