## Methods

### Study design

The study design was a randomized, controlled, open-label trial comparing the effectiveness of two vitamin D_3_ dosing strategies (monthly vs. daily) on vitamin D status and markers of bone health in adults with diabetes and nephropathy over a 6 month period. Patients were randomized to one of the two vitamin D_3_ supplementation strategies in blocks of 30 using a random number generator (http://www.randomizer.org) by one graduate student (SJ): once monthly (40,000 IU/m; n = 60) or once daily (2,000 IU/d; n = 60) for six months. All members of the research team (with the exception the graduate students (SJ/MH)) were blinded to study allocation. Both vitamin D supplements contain vitamin D_3_ (cholecalciferol) in gel capsule form; Jamieson Natural Sources® Vitamin D 1,000 IU Soft gel (NPN 80017530), and EURO-Pharm International Canada Inc.® EURO D 10,000 IU (DIN 02253178). The two dosing regimens were: 2 capsules of 1,000 IU vitamin D daily (total dose = 2,000 IU/d), or 4 capsules of 10,000 IU vitamin D at the end of each month (total dose = 40,000 IU/m). The daily dose was selected based on results from findings that showed that patients with diabetes with stage 3–4 CKD in Northern Alberta where supplementation with 1000 IU/D vitamin D3 resulted in serum increases of 25(OH) vitamin D less than 25 mmol/L [5,7]. A monthly dose of 40,000 IU/m vitamin D_3_ was chosen to achieve equivalent supplementation to daily dosing assuming an adherence rate of 69%, and with the goal of obtaining a serum 25(OH)D concentration of 100 nmol/L [27,32].

This study was approved by the Human Research Ethics Board at the University of Alberta (File Number: Pro00022639), has received a “No Objection Letter” from Health Canada (Control File Number 148625), and is a registered clinical trial (NCT01476501). The study was monitored by a Drug and Safety Monitoring Board (DSMB) with annual safety reports submitted as per Health Canada protocol. Reporting of study results will be according to the CONSORT (Consolidated Standards of Reporting Trials) Guidelines [33].

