### Secondary outcome variables

#### Participant acceptance and adherence survey

Participants completed a validated survey developed to assess adherence to drug therapy in adults with chronic disease (e.g. hypertension) that has been adapted for our specific therapy [37]. This survey consists of open and close-ended questions. This was used to assess and compare adherence to the two different dosing strategies, and consider participants’ preferences and perceptions of their supplementation strategy. Adherence to the dosing regimens was also assessed by pill counts (at 3 and 6 month visits).

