Continuous and categorical variables (e.g. 25(OH)D, lab parameters, BMD T-scores, adherence scores) were quantitatively analyzed, and open-ended questions regarding participants’ perceived facilitators and barriers were categorized into key themes. Bivariate and univariate analysis were done to assess the potential effect of these variables on vitamin D status and bone health (bone turnover markers).Variables shown to be associated with a poor vitamin D status were assessed using multivariate logistic regression models to determine risk for development of vitamin D deficiency and poor bone health. Regression analysis was also conducted to assess correlation between biochemical parameters (PTH, 25(OH)D, 1,25(OH)_2_D, calcium, phosphorus, magnesium, albumin, eGFR, RBG) and bone turnover markers. Analysis of variance was performed to assess for significant differences in vitamin D status and bone turnover markers over the intervention period in both groups. Regression analysis was performed with serum 25(OH)D and plasma PTH as categorical variables; e.g. 25(OH)D sorted by greater/less than 75 nmol/L and plasma PTH sorted by greater/less than 7.15 pmol/L, the optimal concentrations for bone health [5,26]. Where necessary, vitamin D was adjusted for potential confounding variables (e.g. age, gender, ethnicity, disease severity) using an analysis of co-variance. When adherence to daily vitamin D dosing regimen was greater or less than 69%, the variation in compliance was also accounted for in an analysis of co-variance. For variables demonstrating skewed distributions a logarithmic transformation was used to normalize the data.

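### The ANCOVA that accounts for compliance conditions on a post-randomisation mediator, so a monthly-versus-daily contrast taken from it would not be the effect of the dosing strategy

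*Protocol article*

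**What the plan says.** All references are to the protocol article.

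- **Statistical analysis, main comparison.** Differences between daily and monthly dosing over the intervention period are assessed by repeated measures ANOVA with Bonferroni-corrected pairwise tests. Data are analysed on intention-to-treat and per-protocol bases. No adherence covariate is named.
- **Statistical analysis, covariance analysis.** Later in the section: "Where necessary, vitamin D was adjusted for potential confounding variables (e.g. age, gender, ethnicity, disease severity) using an analysis of co-variance". The next sentence adds "When adherence to daily vitamin D dosing regimen was greater or less than 69%, the variation in compliance was also accounted for", again in an analysis of covariance.
- **Hypotheses, no. 2.** Monthly dosing "will result in improved patient adherence and satisfaction with vitamin D_3_ supplementation when compared to daily dosing", "resulting in improved overall vitamin D status, bone health parameters, and quality of life".
- **Participant acceptance and adherence survey**, under secondary outcomes. Of the survey: "This was used to assess and compare adherence to the two different dosing strategies". Pill counts at 3 and 6 months supplement it, for both regimens.
- **Study design.** The monthly dose "was chosen to achieve equivalent supplementation to daily dosing assuming an adherence rate of 69" per cent.

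**The concern.** The covariance rule treats compliance like age, gender, ethnicity and disease severity, that is, as a confounder to be adjusted away. Adherence is different in kind. It arises after allocation, the trial expects allocation to change it, and the second hypothesis makes it the link from dosing strategy to vitamin D status. Holding it constant blocks the pathway that this hypothesis sets out to test. If an unmeasured factor, such as general health behaviour, drives both adherence and 25(OH)D, conditioning on adherence also destroys the balance that randomisation provided.

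The rule is also poorly fixed. A condition of being above or below 69% excludes only the single value 69%, so it does not say when the adjustment applies. It refers to the daily regimen alone, which leaves open what is entered for monthly patients.

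At stake is the possibility that a contrast from this model is reported as the answer to the monthly-versus-daily question.

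**Working it through.** **1. The causal order in the document.** Hypothesis 2 gives arm → adherence → vitamin D status. The outcome section lists adherence as an outcome compared between arms. The covariance rule then conditions on it. A model with arm and adherence as terms estimates an arm contrast at fixed adherence, not the total effect of the strategy.

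**2. The origin of 69%.** Daily arm over a 30-day month: 2,000 × 30 × 0.69 = 41,400 IU, against 40,000 IU monthly. The two match, given whole 10,000 IU capsules. The equivalence therefore depends on adherence differing between arms, and equalising adherence statistically undoes it.

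**3. What that does in nmol/L, without simulation.** The response is 25 nmol/L per 1,000 IU/day (Sample size section; linearity is assumed), that is 0.025 per IU/day. The monthly dose is 40,000 / 30.4375 = 1,314 IU/day.
- 69% daily adherence, full monthly adherence: 0.025 × (1,314 − 2,000 × 0.69) = 0.025 × (−66) = −1.6 nmol/L.
- Equal adherence of 69%: 0.025 × 0.69 × (1,314 − 2,000) = −11.8 nmol/L.

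**4. Simulation of the adjusted contrast (monthly minus daily).** 4,000 trials, 60 per arm, mean daily adherence 69%, same response. Assumed, not in the document: beta-distributed adherence (parameters summing to 8), residual SD 20 nmol/L, and the monthly adherence levels. The common-cause version adds a factor worth 10 nmol/L per SD, correlated about 0.6 with the adherence ranking.

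| Mean monthly adherence | True total effect | Adjusted for continuous adherence | Same, with common cause |
|---|---|---|---|
| 69% | −11.8 | −11.7 | −11.8 |
| 80% | −8.2 | −12.9 | −17.4 |
| 90% | −4.9 | −14.3 | −23.2 |
| 97% | −2.6 | −16.0 | −28.0 |

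The unadjusted contrast recovers the true effect to within 0.1 in every row. The shifts (adjusted minus true) are:
- 80%: −12.9 − (−8.2) = −4.7; with the common cause, −9.2.
- 90%: −9.4; with the common cause, −18.3.
- 97%: −13.4; with the common cause, −25.4.

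**5. Other readings of the covariate.** Values are without / with the common cause.
- *Below-69% indicator in both arms:* −11.1 / −13.8 at 80%, −9.9 / −14.0 at 90%, −8.3 / −12.7 at 97%. The shifts run from about 3 to 10. At equal adherence there is none (−11.7 / −11.8).
- *Below-69% indicator in the daily arm only:* even at equal adherence of 69%, −11.8 becomes −17.5 / −21.9, because all monthly patients are compared with well-adherent daily patients. At 80% to 97% the shift is about 6 / 10.

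The document states no figure for this adjustment, so there is none to reproduce.

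**The case against.** The strongest reply is that the main comparison is untouched. The repeated measures ANOVA is planned on an intention-to-treat basis with no adherence covariate named. The compliance sentence comes late in a passage that is mostly about risk factors and correlations, and the text does not say that this ANCOVA estimates the arm effect or replaces the main analysis. That stands, and it limits the point. A reader might infer that the plan's treatment comparison as a whole is adherence-adjusted, or that no intention-to-treat estimate will exist. The document supports neither. Nor is the lack of a stated ranking of analyses a fault in a condensed article.

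It is also fair that adherence is measured in both arms. A reader might infer that the covariate cannot be defined for monthly patients, but only the trigger is limited to the daily regimen. The trigger may have been meant as a check should observed daily adherence depart from the design assumption, or as a split at 69%. Either is plausible. Neither is what the sentence says, and under either the covariate remains a post-randomisation mediator.

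Finally, the magnitudes rest on assumptions. It is tempting to set them against a detectable difference of about 14 nmol/L. That figure needs an SD near 25 nmol/L with 51 evaluable patients per arm (60 × 0.85). The Sample size section gives no SD and plans for change from baseline within each group, so 14 is not a stated property of this trial.

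What remains is that the article states a rule that puts compliance in a covariance model alongside confounders, and does not mark it as unsuitable for the arm contrast.

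**Conclusion.** The point holds for the adherence-adjusted ANCOVA and for nothing wider. Any monthly-versus-daily contrast from that model would not estimate the total effect of the dosing strategy, and the rule for applying it is not usable as written.

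The size is illustrative. With continuous adherence as the covariate, 69% daily adherence and 80% to 90% monthly adherence, the shift is roughly 5 to 18 nmol/L against the monthly arm. The lower end is without a common cause of adherence and outcome, the upper end with one. Over every covariate form simulated with monthly adherence above 69%, the shift runs from about 3 to 25 nmol/L.

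The direction for a symmetric adjustment depends on monthly adherence being higher, as the trial hypothesises. With equal adherence a symmetric adjustment gives about no shift, and only a daily-only covariate still distorts the contrast. The methodological conclusion needs none of these assumptions, since it follows from hypothesis 2 and the outcome list.

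**What to change.** Reword the compliance sentence in the Statistical analysis section to say that:

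1. the intention-to-treat repeated measures comparison, without adherence adjustment, answers the monthly-versus-daily question;
2. adherence does not enter any model that estimates that effect;
3. adherence is reported by arm as the secondary outcome it already is;
4. any analysis relating intake or adherence to 25(OH)D is exploratory, is labelled so, and uses the same adherence definition in both arms, without the 69% trigger.

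The cost is a sentence or two of analysis wording. No patients, visits or measurements are added, since pill counts already cover both arms. The Discussion describes analysis as ongoing, so the wording can still guide what is reported.

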### Data management and validation

Prior to data entry, these individuals underwent ethics training and evaluation related to protecting participant information and health, including online University of Alberta and National Institute of Health ethics training and testing, criminal record checks, and ensuring up-to-date immunizations. Source data was coded and kept in a locked filing cabinet within the Clinical Research Unit, University of Alberta. Electronic files were encrypted and kept in a password protected computer according to University of Alberta (Faculty of Medicine) encryption policy [49].

The electronic data was audited in a timely manner to ensure any discrepancies were addressed and the potential for future discrepancies was reduced. A variety of standard operating procedures (SOP) were developed to support data analysis. Discrepant results were compared with source records, and amendments were made to the electronic records as necessary. All data entry was cross verified by one trained volunteer/graduate student, along with the primary graduate students involved in the project.

## Discussion

Vitamin D is a nutrient of concern for individuals with diabetes and nephropathy, particularly for those living in northern climates with limited sunlight exposure. Dietary restriction of vitamin D-rich food sources (e.g. dairy products) is a common issue due to concerns around phosphorus, potassium and carbohydrate content. Avoidance of sunlight is also common due to instructions for concomitant medications. Vitamin D supplementation is required in this population, yet the most effective dose and most efficient dosing strategy is unknown. Low adherence rates to routine vitamin D supplementation is also an inherent challenge and therefore developing alternative approaches such as alterations in dosing frequency (monthly verses daily) is also an important consideration [26]. Previous studies have been limited by small sample size, short intervention duration or retrospective design. This study prospectively investigated the impact of two different oral vitamin D_3_ supplementation dosing strategies (2,000 IU/d vs. 40,000 IU/m) for 6 months on markers of vitamin D status and bone health in a large group of adults with diabetes and nephropathy.

Measurement of markers of dynamic expression of bone turnover, enables evaluation of changes over time versus assessment of static changes in bone physiology that could be observed via DXA [50] is a conferred added strength. Markers of collagenous bone resorption (e.g. serum NTx), bone formation (e.g. serum BAP and OC), and the bone-kidney axis/mineral homeostasis (e.g. plasma FGF-23) will allow for exploration of dynamic bone remodeling during vitamin D supplementation. These markers have also been suggested as valuable tools for assessing adherence to bone health therapies [51].

Conferred additional strengths to the study design include the evaluation of socio-demographic, co-morbidities, concomitant medication use and quality of life factors; all factors known to influence adherence to vitamin supplementation. Ongoing analysis will enable a comprehensive evaluation of both lifestyle and physiological factors that influence response to vitamin D supplementation in this population. Dietary intake will be analyzed using validated methodologies for its contribution to total vitamin D intake and status, as well as intake of other nutrients that are known to impact bone health (e.g. calcium, magnesium, phosphorus). Finally, participants were enrolled throughout two calendar years, thus accounting for seasonal variations in vitamin D status. They completed sunlight exposure and weight-bearing physical activity questionnaires at each appointment so that potential impact of sunlight exposure during the different seasons as well as indoor and outdoor activity can be assessed for impact on vitamin D status and BMD.

Increasing evidence suggests that current recommendations for vitamin D intake are inadequate, particularly for populations at risk for suboptimal vitamin D status, such as those with diabetes, kidney disease or living in northern climates [3,5,7,27]. Moreover, the need for RCTs assessing higher doses of vitamin D_3_ supplementation at varying frequencies of administration and its impact on bone health in this population is supported by the research community [3,12,27,35,52,53]. The present study will help fill this gap in the literature, and elucidate an appropriate vitamin D_3_ supplementation dose for improved vitamin D status and bone health in adults with diabetes and nephropathy [12,27,35,52,53].

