### Participants

Patients were recruited from Northern Alberta Renal Program (NARP) clinics at Alberta Health Services (AHS) in Edmonton, Alberta between November 2011 and December 2013. This is a multidisciplinary program (endocrinologists, nephrologists, registered nurses (RN), registered dietitians (RD), pharmacists and social workers) that provides care to over 1,500 patients with diabetic nephropathy in northern Alberta. Sixty adults with diabetes and nephropathy per vitamin D_3_ supplementation group were recruited into this study (n = 120 total). Potential participants were approached by a member of the clinical team (e.g. RD or RN) and asked if a research team member could discuss this study with them. If verbal consent was provided, then a research team member contacted the patient, explained the study to them and determined their eligibility for participation in this RCT; if eligible and agreed by the patient, informed consent was signed and the baseline study appointment was booked. Subsequent study visits (e.g. 3 month and 6 month follow-up appointments) were booked via telephone calls made approximately 2 months later to follow-up with the participants and address any questions or concerns they may have had about their supplement strategy. Patient eligibility for this RCT was determined upon information available in the medical chart at time of screening. Inclusion/exclusion criteria are as follows:

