### Data collection

Assessment of vitamin D status, bone health and lifestyle factors (diet, physical activity, sunlight exposure, QoL) were performed during study visits at the Clinical Research Unit (CRU) at the University of Alberta at baseline, 3 and 6 months post study enrolment between January 2012 and June 2014. Participants were given a 3 month supply of their respective vitamin D_3_ supplementation strategy at baseline and again at the 3 month study visit. They were asked to return their vitamin D_3_ vials/pill containers to the study investigators at the 3 and 6 month study visits. At baseline, information related to patient demographics and anthropometrics was collected. This included age, gender, ethnicity, medications/supplement use, insulin regimen, height, weight (Health O-Meter Professional model 597KL, Pelstar LLC, Alsip, IL, USA) and BMI. Changes in these variables between appointments were documented (e.g. medications, height, weight). Bone mineral density (BMD) was measured at baseline using Dual-energy X-ray Absorptiometry (DXA); a validated tool to assess BMD (General Electric LUNAR Prodigy, version 10.5, Madison, WI, USA). Whole body scans as well as site specific scans of the lumbar spine (L1-L4) and left total hip (including femoral neck) were conducted. The precision error, expressed as a percentage coefficient of variation (%CV), for the Lunar DXA located in the CRU are as follows: whole body BMD 0.7%, lumbar spine 0.9% and total hip 1.2%.

Lifestyle factors were assessed at baseline, 3 and 6 months using validated tools [35-41]. These include: 1) 3-day food record to assess vitamin D and calcium intake and other dietary factors known to influence vitamin D and bone health (phosphorus, carbohydrates, protein, caffeine). Dietary intake was analyzed using the Food Processor Database (Food Processor SQL, v.10.8, ESHA Research, Salem, Oregon, USA); 2) Weight-bearing physical activity records; 3) Sunlight exposure questionnaires; 4) Health related QoL (SF-36) questionnaires (http://www.qualitymetric.com Liscence Number QM019185 OPTUMInsight^TDM^); and 5) Adherence and acceptance surveys [34-38,42-44]. Adherence to vitamin D_3_ supplementation was also assessed by pill counts of returned vitamin bottles at 3 and 6 months.

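### Enrolling over two calendar years can balance season on average but does not account for it, and the stated 25(OH)D treatment model has no season term

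*Protocol article*

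**What the plan says.** Among the strengths of the design, the Discussion states: "participants were enrolled throughout two calendar years, thus accounting for seasonal variations in vitamin D status".

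The parts of the article that bear on this claim are:

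- **Calendar.** Participants says that patients were recruited "between November 2011 and December 2013". Data collection places the visits "at baseline, 3 and 6 months post study enrolment between January 2012 and June 2014".
- **Arms.** Study design allocates patients to "once monthly (40,000 IU/m; n = 60) or once daily (2,000 IU/d; n = 60) for six months". Both arms are supplemented and there is no untreated arm.
- **What is tested.** Hypothesis 1 expects serum 25(OH)D to rise by at least 25–50 nmol/L and bone markers to change "after 6 months of vitamin D_3_ supplementation when compared to baseline levels". The Sample size section also rests on change from baseline in each group.
- **Treatment model.** Statistical analysis compares dosing types over time by repeated-measures analysis of variance, then Bonferroni-corrected pairwise t-tests within and between groups. Season is not among the terms.
- **Adjustment.** Where it is judged necessary, vitamin D is "adjusted for potential confounding variables (e.g. age, gender, ethnicity, disease severity) using an analysis of co-variance". The list is illustrative and mentions neither season nor sunlight.
- **Sunlight data.** A sun-exposure questionnaire is completed at each visit to help allow for season. In Statistical analysis, sunlight exposure appears only among possible risk factors for insufficiency and poor bone health.

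**The concern.** Background says that winter sun contributes little to vitamin D status in northern climates, so the document itself treats season as relevant to the primary outcome. A follow-up of 6 months is the interval at which a yearly cycle moves a patient's value most: a patient who starts at the seasonal low finishes near the high, and the reverse.

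Spreading enrolment over whole years can make these shifts cancel in the mean. It cannot remove them from individual changes, so without a season term they stay in the residual. At stake are the precision of the daily versus monthly comparison and the reading of within-arm rises as an effect of the supplement, since no untreated arm shows what season alone would have done.

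**Working it through.** The plan gives no seasonal figure to reproduce, so the check uses assumed amplitudes.

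**Inputs from the document**
- Visits at 0, 3 and 6 months, from January 2012 to June 2014. Baselines therefore fall in about January 2012 to December 2013, or 24 months.
- 60 patients per arm and 15% attrition: 60 × 0.85 = 51 evaluable per arm.
- α = 0.05, taken as two-sided, and power 0.80 (the document's β = 0.8 is read as power).
- The only SDs of 25(OH)D given are 15 (before) and 25 (after) nmol/L, from a cited study of 1,000 IU/d for three months.

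**Assumptions, not in the document**
- A yearly curve s(t) = A·cos(2π(t − peak)/12), with mean-to-peak amplitude A = 5, 10 or 15 nmol/L.
- A pre–post correlation of 0.5, so SD of change = √(15² + 25² − 2 × 0.5 × 15 × 25) = √475 = 21.8 nmol/L. This is treated as free of seasonal variance.

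**Step 1: one patient.** Since s(t + 6) = −s(t), the seasonal part of the 6-month change is −2s(t). It can reach ±2A, that is ±10 to ±30 nmol/L.

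**Step 2: mean under even accrual.** Over two full cycles the mean of −2s(t) is 0. To this extent the Discussion sentence is right.

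**Step 3: variance under even accrual.** Var(−2s) = 4A² × ½ = 2A². The detectable between-arm difference in 6-month change is 2.8016 × SD × √(2/51).

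| A (nmol/L) | Added variance 2A² | Total variance | Ratio to 475 | SD | Detectable difference |
|---|---|---|---|---|---|
| 0 | 0 | 475 | 1.00 | 21.8 | 12.1 |
| 5 | 50 | 525 | 1.11 | 22.9 | 12.7 |
| 10 | 200 | 675 | 1.42 | 26.0 | 14.4 |
| 15 | 450 | 925 | 1.95 | 30.4 | 16.9 |

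In sample-size terms, 51 per arm would carry the information of 51 × 475/525 = 46 (A = 5) to 51 × 475/925 = 26 (A = 15) patients free of seasonal variance.

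The correlation matters less than A. At 0.7 (variance 325) the detectable difference goes from 10.0 to 10.7–15.4 nmol/L. At 0 (variance 850) it goes from 16.2 to 16.6–20.0 nmol/L.

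**Step 4: within-arm mean under uneven accrual.** The mean of |cos| is 2/π. If a share p of baselines falls in one half-year, centred on the seasonal low or high, the mean change shifts by (2p − 1) × 2A × 2/π. For p = 0.65:
- A = 5: 0.30 × 10 × 0.637 = 1.9 nmol/L
- A = 15: 0.30 × 30 × 0.637 = 5.7 nmol/L

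That is 8–23% of the 25 nmol/L minimum rise. It inflates the rise if the low half-year is over-represented and deflates it otherwise.

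**Step 5: between arms.** Patients are randomised concurrently and both arms share the calendar, so the expected seasonal difference between arms is 0 whatever the accrual pattern.

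**The case against.** The strongest reply has three parts.

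**Baselines cover about two full cycles.** The seasonal shift then averages out and the sentence is correct for the mean change. This stands if accrual was even, but the article does not report accrual by month. Averaging out also leaves the variance of Step 3 untouched.

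**Season is partly handled.** Sunlight exposure is recorded at every visit, it enters the analyses of factors related to vitamin D status, and the covariate list is open. So it would be wrong to infer that season has been excluded from the analysis. Still, the article commits to no season or sunlight term in the model that estimates the treatment effect, and adjusting only where necessary fixes nothing in advance.

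**An article may leave covariates to a statistical analysis plan.** That is fair as to the full list and its coding. The point here is narrower: the article states its treatment model and separately says that the enrolment pattern takes care of season, and the second statement does not follow from the design.

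Two stronger readings are tempting and are not supported. A reader might infer that season biases the daily versus monthly contrast; concurrent randomisation rules that out in expectation. A reader might also infer that blocks of 30 leave the arms unbalanced on season. How well such blocks balance it depends on where the seasonal peak falls relative to the block boundaries, which the documents do not show, and any imbalance would be chance rather than bias.

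**Conclusion.** The point holds in limited form. Year-round enrolment at best balances season on average; it does not account for it.

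- **Daily versus monthly comparison:** no expected bias, but a loss of precision that arises even with perfectly even accrual. The detectable difference rises by 0.6 nmol/L (A = 5) to 4.8 nmol/L (A = 15).
- **Within-arm change:** biased only if accrual is uneven over the year. The documents do not show that it was, so the 1.9–5.7 nmol/L is an illustration. Even its upper end is under a quarter of the minimum rise of 25 nmol/L.

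The amplitude, the correlation and the 65% share are all assumptions. The SDs come from a cited study with another dose and duration; if they already contain seasonal spread, the added variance is overstated. The point does not threaten the trial's validity, but the remedy is nearly free and should be adopted.

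**What to change.** 1. In the 25(OH)D treatment model, include the calendar date of each draw as a pre-specified covariate, either as sine and cosine of day of year or as season. Because it changes by visit, use a mixed-model form of the repeated-measures analysis. Enrolment across two cycles helps here, since it lets the model separate season from time on study.
2. Report within-arm change adjusted for this term, and say that without an untreated arm the change is not a pure supplement effect.
3. Reword the Discussion sentence to say that year-round enrolment balances season on average and that the model adjusts for what remains.

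The Discussion describes analysis as ongoing. If the 25(OH)D comparison has already been run, report the adjusted model as an added analysis and label it so.

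The cost is about 2 degrees of freedom, from visit dates that the study already holds. How much precision is regained depends on how well the curve fits.
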